### Trial Design

The study is a multicenter, prospective, single-blinded, parallel group, and 1:1 individually randomized controlled trial. The study duration is 48 months (maximum), with recruitment starting at month 5 and postdischarge follow-up starting at month 11. We aim to enroll between 90 and 130 participants over a 24-month recruitment period. The study pathway is shown in Figure 1.

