### Sample Size

Recruitment will continue for 24 months. We expect to enroll between 90 and 130 participants. Sample size was based on the 2 clinical outcomes: the rate of healing and time to complete re-epithelialization. We expect at least 70% of ulcers to heal within 84 days with standard care (according to a recent study of neuropathic ulcers, with over half due to leprosy [16]). If we assume that the intervention will increase this proportion to 90% and hazards are constant and proportional (so that the hazard ratio is 1.91 for discharge), for a 2-sided test of the hazard ratio with a type I error of 5%, a statistical power of 80%, and a 1:1 allocation ratio, 47 individuals are required in each group. With 130 participants, this allows for a dropout rate of up to 40% to achieve a power of 80%. At the most pessimistic sample size of 90, with a dropout rate of 40%, our minimum detectable effect size (ie, the effect size that achieves a power of 80% with 33 patients per arm) is a hazard ratio of 2.15, or 92.5% of patients in the treatment group being discharged by the end of the trial period. At the most optimistic sample size of 130 with no dropout, our minimum detectable effect size is a hazard ratio of 1.74, or 87.3% of patients being discharged in the treatment group. All calculations are based on a log-rank test.

We took a conservative approach and based the sample size calculation on the healing outcome and model with lower efficiency to ensure an adequate sample size for all main outcomes, since our inferential approach is not based on statistical significance but on a consideration of effect sizes and a comparison and triangulation of the totality of evidence. We are not particularly concerned with being “overpowered” or with a problem of multiple comparisons; instead, we will focus on ensuring a sufficient sample size to estimate clinical effectiveness to a reasonable degree of precision [17,18].

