### Statistical Methods

#### Statistical Methods for Primary and Secondary Outcomes

Time to healing will be analyzed using a Cox proportional hazards model with and without adjustment for baseline characteristics (trial ulcer area and participants’ age), allowing for right censoring. For the rate of healing, we will define the outcome ulcer size in cm^2^ at each time point and include in the model time since admission, treatment status, and their interaction. We will analyze this model using a linear mixed-effects model with participant-level random effects and both with and without adjustment for participant characteristics. Given there are multiple clinical outcomes (2 outcomes, with and without adjustment), we will adjust reported *P* values for multiple testing using a step-down method, which provides an efficient means of controlling the family-wise error rate [22]. We will derive the approximate distributions of the test statistics to perform the step-down procedure using a permutation test approach, by simulating 10,000 rerandomizations of the individuals [23].

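### The 80% power at 47 per group is for one test at 5%, but the analysis section adjusts P values over four tests and names no ruling model per outcome

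*Protocol article*

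**What the plan says.** The Sample Size section sizes the trial on time to healing. Its control assumption is "We expect at least 70% of ulcers to heal within 84 days with standard care". Its effect assumption is "If we assume that the intervention will increase this proportion to 90% and hazards are constant and proportional (so that the hazard ratio is 1.91", the sentence then referring to discharge. The calculation is "for a 2-sided test of the hazard ratio with a type I error of 5%, a statistical power of 80%, and a 1:1 allocation ratio", giving 47 per group by a log-rank test. The same section says that inference will rest on effect sizes and the totality of evidence rather than on significance, and that the authors are not much concerned with being overpowered "or with a problem of multiple comparisons".

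The section Statistical Methods for Primary and Secondary Outcomes analyses time to healing by Cox regression "with and without adjustment for baseline characteristics (trial ulcer area and" age. Rate of healing is analysed by a linear mixed model, also in both forms, with adjustment covariates that are not named. The multiplicity rule begins "Given there are multiple clinical outcomes (2 outcomes, with and without adjustment", and all reported P values are then adjusted by a step-down method that controls the family-wise error rate, with 10,000 simulated rerandomizations. Neither form of either model is called primary.

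The Interim Analyses section reuses these methods and applies a one-sided 0.01 (two-sided 0.02) threshold to either of the two primary outcomes.

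**The concern.** The power statement and the testing rule describe different trials. Power is given for one unadjusted test at 5%. The P values to be reported come from a stricter rule over four tests, so a reader who takes the 80% at face value is misled about what the reported P values can show at that sample size.

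The two sections also disagree on whether multiplicity matters: one sets it aside and the other builds a permutation procedure to control it.

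Finally, the adjusted and unadjusted versions of a model ask the same question about honey. Putting both in the family leaves two answers per outcome and no rule for choosing when they differ. The gap reaches the interim look, where it is undefined which model's result counts as crossing the threshold for an outcome.

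**Working it through.** **Inputs from the Sample Size section:** 70% versus 90% healed by 84 days, hazard ratio 1.91, two-sided 5%, 80% power, 1:1 allocation, 47 per group, enrolment of 90–130.

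**Step 1: reproduce the stated figure.**
- Hazard ratio: ln 0.10 / ln 0.30 = 1.912.
- Schoenfeld events: 4 × (1.960 + 0.842)² / (ln 1.91)² = 75.
- Per arm: 75 / (0.70 + 0.90) = 46.9, so 47.
- Expected events at 47 per arm: 47 × 1.6 = 75.2. Noncentrality: √75.2 / 2 × ln 1.91 = 2.81. Power: Φ(2.81 − 1.96) = 80.1%.

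The 47 is therefore correct for a single test at 5%.

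**Step 2: bounds that need no correlation assumption.** Using power = Φ(2.81 − z):
- Bonferroni over two tests (alpha 0.025, z = 2.24): 71%, or 72% with the unrounded hazard ratio of 1.912. Restoring 80% takes 57 per arm.
- Bonferroni over four tests (alpha 0.0125, z = 2.50): 62%. Restoring 80% takes 67 per arm.

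**Step 3: the step-down itself.** The document gives no correlations and no effect size for rate of healing, so these are assumptions: correlation 0.85–0.95 between adjusted and unadjusted tests of one outcome, 0.5–0.7 between outcomes, and noncentrality 2.81 for both Cox tests. The largest |Z| is compared with the 95th percentile of the maximum over all tests, then the next largest with the maximum over those remaining, and so on (400,000 draws per setting). The first-step critical P for four tests is 0.017–0.022.

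| Effect on rate of healing | Given Cox test, four-test family | Cox test, two-test family |
|---|---|---|
| None | 68–71% | 73–74% |
| Equally strong (noncentrality 2.81) | 73–75% | 77% |
| Stronger (noncentrality 3.5) | 76–77% | 79% |

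Both columns are full step-down power, so they compare like with like. The duplicates cost about 2–5 points. The rest of the drop from 80% comes from having two outcomes.

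**Step 4: two answers per outcome.** Under the same assumptions, the adjusted and unadjusted Cox tests reach opposite verdicts in about 5–13% of simulated trials.

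**Step 5: the top of the enrolment range.** With 65 per arm and no dropout there are 65 × 1.6 = 104 events and the noncentrality is 3.30. Power is 91% at alpha 0.05, 84% at 0.022, 81% at 0.016 and 79% at 0.0125.

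**The case against.** - **Inference is not meant to rest on significance.** The Sample Size section says so, and this lowers the stakes. It does not remove the inconsistency: the same section claims 80% power at 5%, the analysis section adjusts P values, and the interim rule acts on P-value thresholds.
- **Sizing was conservative.** The authors say they sized on the less efficient outcome and model, so they expect the other tests to be stronger, and a step-down then gives power back. This stands, and it is why the favourable rows of the table matter. Even there the figure is 76–77%, not 80%.
- **The duplicate test is not purely a cost.** With an equally strong rate effect, at least one of the two Cox tests rejects in about 77–78% of simulated trials, against 77% for the single Cox test in a two-test family. This also stands, but it helps only if either model may carry the claim, and the protocol does not say that.
- **The ruling model could be left to the statistical analysis plan.** That is fair for covariate detail. Here the protocol itself fixes both the four-test family and the power figure that disagrees with it.
- **Hospital.** A reader might infer that leaving hospital out of the named Cox covariates contributes to the shortfall, since the Trial Design section says "The study is a multicenter, prospective, single-blinded, parallel group, and 1:1 individually randomized controlled trial" and randomization is stratified only by ulcer size. The document does not support that. It gives no outcome difference between hospitals, the mixed model's covariates are unnamed, and an analysis without a factor that was not a stratum remains valid.

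**Conclusion.** The stated 80% at 47 per group is right for one test at 5% and is not what the protocol's own testing rule delivers. Under that rule, power for a given Cox test at 47 per arm is about 68–77%, depending on the effect on rate of healing, with a Bonferroni floor of 62%. The 68–77% range rests on the assumed correlations and rate effects; the floor does not. The conflict between the two sections on multiplicity and the missing ruling model need no assumption.

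Two stronger readings fail. A reader might conclude that the trial is underpowered throughout its planned range, but at 65 per arm without dropout power stays at about 79–84%. A reader might also blame the adjusted/unadjusted duplicates for most of the loss, but they account for about 2–5 points and the second outcome accounts for most of the rest. The point is worth correcting because the remedy is only wording. It does not undermine the design.

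**What to change.** 1. Name one primary model per outcome: the adjusted one, with age and baseline ulcer area, the variable on which randomization is stratified. For the mixed model, state whether the baseline measurement enters as a covariate or as an outcome row.
2. Limit the step-down family to those two tests. Report the unadjusted models as sensitivity analyses outside it.
3. State that the interim threshold applies to the same primary models.
4. Reconcile the multiplicity remark in the Sample Size section with the step-down rule.
5. Restate power at 47 per arm at the level used: about 72% under Bonferroni over two tests, or about 73–79% under the two-test step-down with its assumed correlations and rate effect written out.

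Adding hospital as a two-level covariate is an optional, separate precision choice and should not be presented as a remedy for the power gap.

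The cost is wording in two or three sections and a less favourable power figure. No new data are needed. The change does not restore 80% at 47 per arm, because two outcomes remain.

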#### Interim Analyses

An interim analysis will be conducted when at least 49 (three-eighths [37.5%] of the 130 target) participants have been followed up for of 84 days or discharged, whichever comes first. The rationale for this analysis is the detection of a “penicillin-like” benefit or statistically significant negative effect of the treatment on either primary outcome. The statistical methods will be as specified above. A statistical threshold of 0.01, one-sided (0.02, two-sided), will be used for either primary outcome. If either threshold is exceeded, or if the Independent Data Monitoring Committee (IDMC) has other concerns, then the Trial Steering Committee (TSC) will be advised accordingly. If the IDMC wishes to meet again before trial conclusion, they will be able to do so. Only the trial statistician and the IDMC will see the “unblinded” data, unless the TSC is informed.

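### The interim benefit threshold (two-sided 0.02) is too lenient for a penicillin-like effect, and the protocol states no allowance for the look in the final test

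*Protocol article*

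**What the plan says.** The Interim Analyses section of the protocol article places the look when at least 49 participants (three-eighths of the 130 target) have completed 84 days or been discharged. It gives two purposes: finding a penicillin-like benefit, and finding a statistically significant negative effect, on either primary outcome. One threshold serves both: "A statistical threshold of 0.01, one-sided (0.02, two-sided), will be used for either primary outcome". The consequence is advisory. "If either threshold is exceeded", or if the data monitoring committee (IDMC) has other concerns, the Trial Steering Committee (TSC) is advised. The IDMC section adds that the committee advises on whether continued recruitment is justified and that the TSC decides.

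The Sample Size section plans "for a 2-sided test of the hazard ratio with a type I error of 5%, a statistical power of 80" percent and concludes that with "a 1:1 allocation ratio, 47 individuals are required in each group". The Statistical Methods section adjusts reported P values by a step-down permutation method across two outcomes, with and without covariates. It does not mention the interim look.

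**The concern.** A penicillin-like benefit is one so large that continuing would be hard to defend. A threshold for it should be out of reach of an effect of ordinary, planned size. A two-sided 0.02 with 49 participants does not look like that.

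Two things are at stake. First, an estimate that crosses must already be at least about HR 2.10. A trial stopped on it would tend to report an exaggerated effect from 49 people. Second, the same data are tested again at the end, and the article does not say that the final level is reduced to allow for this.

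**Working it through.** **Inputs**
- Control healing by 84 days: "We expect at least 70% of ulcers to heal within 84 days with standard care".
- Intervention: "If we assume that the intervention will increase this proportion to 90" percent.
- Planning effect: "the hazard ratio is 1.91 for discharge". Check: ln(0.1)/ln(0.3) = 1.912.
- Interim at 49 participants; enrolment 90 to 130; dropout up to 40% (Sample Size, Interim Analyses).

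**1. Reproducing the plan's sample size**

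Schoenfeld events = 4 × (1.960 + 0.842)² / (ln 1.91)² = 75. Mean healing probability = (0.70 + 0.90)/2 = 0.80. Total = 75/0.80 = 93.75, or 47 per group, as stated. The same formula returns the stated HR 2.15 at 33 per arm and 1.74 at 65 per arm. The interim size also agrees: 3/8 × 130 = 48.75, rounded up to 49.

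**2. Where the benefit boundary falls**

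Expected events at the interim = 49 × 0.80 = 39.2. One-sided 0.01 is z = 2.326. Boundary HR = exp(2 × 2.326/√39.2) = 2.10. With 70% healed on control, this is 1 − 0.3^2.10 = 92.0% on honey.

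The article's minimum detectable HR at its most pessimistic size is 2.15. That is a true effect with 80% power, not a boundary, so the two are not the same quantity. It still shows that an observed 2.10 lies within the range of effects the trial was planned around.

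**3. Chance of crossing for benefit on time to healing**

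P = Φ(√39.2/2 × ln 1.91 − 2.326) = Φ(2.026 − 2.326) = 0.38. A log-rank simulation (20,000 runs, exponential healing times, censoring at 84 days) also gives 38.2%. The simulated figures at other true effects are 27% at HR 1.74 and 53% at HR 2.15.

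At two-sided P<0.001 (z = 3.291), the boundary HR is exp(2 × 3.291/√39.2) = 2.86, and the chance at HR 1.91 is Φ(2.026 − 3.291) = 0.10.

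**4. Overall error for one outcome**

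This assumes that an interim crossing counts as a positive result and that the final test is at two-sided 0.05. The two z-statistics are bivariate normal with correlation √(information fraction). Overall error = 1 − P(|Z₁| < 2.326 and |Z₂| < 1.960).

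| Interim/final | Fraction | Correlation | Overall two-sided error |
|---|---|---|---|
| 49/130 | 0.377 | 0.614 | 6.3% |
| 49/90 | 0.544 | 0.738 | 6.0% |
| 49/78 (130 less 40%) | 0.628 | 0.793 | 5.8% |
| 49/54 (90 less 40%) | 0.907 | 0.953 | 5.1% |

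Counting false benefit only, the 49/130 figure is 3.2% one-sided, against 2.5%.

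**5. The alternatives, one outcome, 49/130**
- 0.001 two-sided in both directions, final 0.05: 5.04%.
- 0.0005 one-sided for benefit and 0.01 one-sided for harm, final 0.05: false benefit 2.52% one-sided; two-sided total including harm crossings 5.7%.
- 0.02 kept: the final two-sided level that holds 5% overall is 0.036 at 49/130 and 0.039 at 49/90.

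**The case against.** The strongest reply is that the look is advisory. A crossing obliges nobody to stop or to claim anything. If it never led to either, the final test would keep its own level. The 5% ("for a 2-sided test of the hazard ratio with a type I error of 5" percent) is a sample-size input, the same section says that inference does not rest on statistical significance, and an analysis plan or IDMC charter that is not shown could set the final level. All of this stands. A reader might infer that the trial's false-positive rate definitely exceeds 5%, but the document supports that only under the two conditions in step 4.

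A reader might also infer a larger inflation because the threshold applies to either of two outcomes. With 0.02 applied to each outcome unadjusted and step-down control only at the end, simulation gives about 7.0% to 8.0% for assumed correlations of 0.9 to 0. But the interim section says that the methods are those already specified, which plausibly brings the step-down into the interim too. The figure is then about 6.3% to 6.4%, so the larger range is not established.

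Nor is an early benefit signal likely at the planning effect: 38% is below one half. It exceeds one half only if the second outcome is assumed to carry an equal standardized effect with low to moderate correlation, and the document gives no figure for either.

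None of this touches the first part of the point. The threshold and its purpose are both written in the interim section, and they do not match whatever the TSC does with the advice.

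**Conclusion.** The point holds in two parts of different strength.

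The mismatch between purpose and threshold is firm. It needs only the article's own healing proportions and the interim size: a boundary at an observed HR of about 2.10, and about a 4 in 10 chance of crossing on time to healing at HR 1.91. It assumes constant, proportional hazards, as the sample size does, and equal arms at the interim.

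The error inflation is conditional and modest. It is 6.3% or 6.0% for one outcome without dropout, down to 5.1% at the highest information fraction that the article's dropout allowance implies. About half of it is the harm side. For a false claim of benefit the excess at 49/130 is about 0.7 percentage points (3.2% against 2.5%).

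**What to change.** In the Interim Analyses section and the IDMC charter, replace the single threshold with two: benefit at two-sided P<0.001 (one-sided 0.0005), and one-sided 0.01 kept as a guideline for harm only. The final test can then stay as it is, with a false-benefit rate of about 2.52%. The text should not claim an overall two-sided error of 5.04% for this pair. That figure needs 0.001 in both directions; counting harm crossings, the total here is about 5.7%.

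If 0.02 is kept for benefit, state a final two-sided level of about 0.036 (49 of 130) to 0.039 (49 of 90), and state that the step-down adjustment across outcomes applies at both looks.

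The change is about one sentence in each document, best made before comparative interim data are seen. Its cost is a lower chance of an early benefit signal at HR 1.91, about 10% instead of 38%, which is what a penicillin-like criterion intends.

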#### Methods for Additional Analyses

We will also compare average daily step count between treatment and control groups as a simple difference in means (1-tailed *t* test). Since 1 group may stay longer in hospital than the other and since there may be an interaction between the rate of healing and step count, we will compare step counts over preset periods at 7, 14, and 42 days.

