### Additional Consent Provisions for the Collection and Use of Participant Data and Biological Specimens

The participant information sheet contains all information about the data to be collected and how the data will be stored and used. Biological specimens such as a swab of the ulcer surface will be obtained for the purpose of screening for bacterial infections prior to the recruitment of a participant into the study. Participants who refuse to give consent will continue to receive normal care from the hospital, but they will not be part of the study.

Participants can decide to withdraw their consent at any time during the study. Such participants will be given a form to complete, stating their reason for withdrawal. A participant may either withdraw fully or they may withdraw from treatment but consent to ongoing data collection.

Once a person consented to participate in the trial, baseline data will be collected. This will precede randomization.

Data will be collected directly onto electronic tablets, and the computer program (Research Electronic Data Capture [REDCap]; Vanderbilt University) will check the range of the information. Photographs of the ulcers will be captured using the tablet device. Each participant will be allocated a unique trial number, which will be included in all data entry forms and linked to the photographs. The level of activity (step count) will be recorded at each dressing change across both intervention and control groups until 84 days or discharge, whichever comes first. This date will enable us to check for postrandomization (“performance”) bias.

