### Relevant Concomitant Care Permitted or Prohibited During the Trial

In line with standard practice, participants will be discouraged from bearing weight on the ulcer site, since weight bearing and the patients’ level of activity might affect the ulcer’s rate of healing. Participants will be asked to wear pedometers on the nonaffected foot, and the level of activity will be recorded on the tablet at each dressing change from the first dressing change until 84 days from randomization or discharge, whichever comes first.

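### The step-count check for performance bias uses a one-tailed t test with no named direction, although an activity imbalance either way would matter (minor)

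*Protocol article*

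**What the plan says.** Three places in the protocol article bear on this point.

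- **Purpose.** The section on additional consent provisions says that recording step counts in both arms "will enable us to check for postrandomization" bias, which it labels performance bias. The section on concomitant care gives the reason activity is of interest: "since weight bearing and the patients’ level of activity might affect the ulcer’s rate of healing".
- **Test.** Methods for Additional Analyses compares average daily steps between the arms "as a simple difference in means (1-tailed" t test). It gives no direction, no alpha and no argument for a single tail.
- **Periods.** The same section anticipates unequal stay ("Since 1 group may stay longer in hospital than the other") and a possible interaction between healing and activity, and answers with fixed periods: "we will compare step counts over preset periods at 7, 14, and 42 days". Step counts are recorded "until 84 days from randomization or discharge, whichever comes first".

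Elsewhere the plan looks both ways. The sample size uses a two-sided test, and the interim rule looks for benefit and harm and states its threshold in both one-sided and two-sided form.

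**The concern.** Participants and the staff who change dressings know the allocation (Researcher Blinding), so activity could differ by arm after randomization. Nothing in the article says which way. If the honey arm rests more, part of any benefit seen could be due to rest. If the honey arm walks more, a real benefit could be hidden. Both are performance bias and both bear on how the main result is read.

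A one-tailed test is built to detect only one of these. Whichever tail is used, an imbalance in the other direction cannot become significant except by rare chance. Because the tail is not named, it could also be settled after the data are seen. At a nominal one-tailed 5%, picking the favourable tail afterwards gives an error rate of 2 × 5% = 10%.

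**Working it through.** **1. The plan's own sample size, as a check on the inputs.** Sample Size assumes "We expect at least 70% of ulcers to heal within 84 days with standard care" and that "the intervention will increase this proportion to 90% and hazards are constant and proportional".

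- Hazard ratio: ln(0.1)/ln(0.3) = 1.912 (the plan gives 1.91).
- Events, Schoenfeld formula, two-sided 5%, 80% power: 4 × (1.960 + 0.842)² / (ln 1.912)² = 75 after rounding up.
- Mean event probability: (0.70 + 0.90)/2 = 0.80, so 75/0.80 = 93.75 in total, or 47 per arm. This matches the plan.

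The step-count comparison has no sample size of its own. I use the per-arm numbers in that section: 47 (the requirement), 33 (its most pessimistic case) and 65 (130/2).

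**2. Power of the step-count test.** The article gives neither an alpha nor a standard deviation for steps. Alpha 5% and true differences d of 0.3 to 0.6 SD are therefore assumptions. With the normal approximation and k = d/√(2/n):

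- one-tailed, chosen direction: Φ(k − 1.645)
- one-tailed, other direction: Φ(−k − 1.645)
- two-sided, either direction: Φ(k − 1.960) + Φ(−k − 1.960)

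For n = 47 and d = 0.5, k = 0.5/√(2/47) = 2.424. This gives Φ(0.779) = 78.2%, Φ(−4.069) = 0.002% and Φ(0.464) + a negligible term = 67.9%.

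| n per arm | d (SD) | One-tailed, chosen direction | One-tailed, other direction | Two-sided, either direction |
|---|---|---|---|---|
| 33 | 0.3 | 33.5% | 0.21% | 23.0% |
| 33 | 0.5 | 65.0% | 0.01% | 52.8% |
| 33 | 0.6 | 78.6% | 0.002% | 68.3% |
| 47 | 0.3 | 42.4% | 0.10% | 30.7% |
| 47 | 0.5 | 78.2% | 0.002% | 67.9% |
| 47 | 0.6 | 89.7% | 0.0003% | 82.9% |
| 65 | 0.3 | 52.6% | 0.04% | 40.2% |
| 65 | 0.5 | 88.6% | 0.0003% | 81.3% |
| 65 | 0.6 | 96.2% | <0.0001% | 92.8% |

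Power in the other direction is below alpha for any d above zero, whatever alpha is used, and it falls as the imbalance grows. The two-sided test gives up 3 to 12 points in the chosen direction across these rows.

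**3. Recorded days in the 42-day period (secondary).** I take the planning hazards as constant and treat healing as discharge, as the sample size section does. The daily hazards are −ln(0.3)/84 = 0.01433 (control) and −ln(0.1)/84 = 0.02741 (honey).

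- Unhealed at day 42: 0.3^0.5 = 54.8% control, 0.1^0.5 = 31.6% honey.
- Mean recorded days up to day 42, (1 − S)/hazard: (1 − 0.548)/0.01433 = 31.6 control, (1 − 0.316)/0.02741 = 24.9 honey.
- The same sum for the first 7 days gives 6.7 and 6.4, and for the first 14 days 12.7 and 11.6.

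Under the planned effect the arms are close at 7 days and about a week of recording apart at 42. If honey has no effect, there is no gap.

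**The case against.** **The difference will be visible anyway.** The plan reports a difference in means, and Sample Size says that inference will rest on effect sizes rather than on significance. A large imbalance in the untested direction would therefore appear in the results with its size and sign. This stands, and it limits the harm. A reader might infer that such an imbalance would be passed off as absence of bias, but the article nowhere says that the P value will be used that way. What remains is that the test specified does not fit the question asked.

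**It is an additional analysis.** It does not enter either main outcome, the step-down adjustment or the interim rule. This also stands, and it sets the severity.

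**The unequal stay is already dealt with.** A reader might go further and infer that the 42-day comparison is made only among those not yet healed, and so between differently depleted arms. The article does not support that. It compares average daily steps, so someone discharged on day 20 can still contribute a daily mean to the 42-day figure. It also gives unequal stay as its own reason for the preset periods. The figures in step 3 of the working need the full planned hazard ratio, constant hazards and healing equated with discharge. They support a caution and do not show that the period is invalid.

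**Day 7 could be made the main comparison.** This would reduce the effect of unequal stay, but it could miss a difference in behaviour that develops later. The article gives no basis for calling its equal treatment of the three periods an error.

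**Conclusion.** The sidedness point holds. A check for bias in which both directions matter is specified with a one-tailed test whose direction is neither named nor justified. That power in the untested direction lies below alpha needs no assumption. The sizes quoted (about 78%, under 0.1%, and 68% for the two-sided alternative) rest on alpha 5%, 47 per arm, a 0.5 SD difference and a normal approximation.

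The 42-day period deserves only a note: about 25 honey against 32 control recorded days per participant, if honey speeds healing as planned and healing means discharge.

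Severity is minor. The main estimates do not depend on this test.

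**What to change.** In Methods for Additional Analyses, replace the one-tailed t test with: *for each preset period (7, 14 and 42 days), the difference between arms in mean daily steps will be reported with a two-sided 95% confidence interval and a two-sided P value.* All three periods stay as they are.

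When the 42-day result is reported, give the recorded days per arm beside it, so that any difference in stay can be seen.

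The change is one sentence and needs no new data. It costs about 10 points of power in one direction at 47 per arm and 0.5 SD (78.2% − 67.9%). In return the test has the same power in the other direction, where it now has almost none.
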